### Randomization and blinding

According to their order of participation in the study, volunteers who sign the informed consent form will be assigned a screening number (e.g., 010,001, 010,002, 010,003, 010,004, 010,005); then, they will receive a serially unique number (e.g., G1001, G1002, G1003, G1004, G1005) according to their screening result. For each of these unique numbers, a random sequence will be generated by the computer software R 4.1.0 and used to randomly assign the unique number (representing a volunteer) to the probiotic group or placebo group. During the study, the subjects and study staff responsible for sample distribution, data collection, data collation and analysis will be blinded to the random sequence, which will be maintained by two independent project managers and unblinded only in the case of important safety issues, and the final data analysis will be completed. Moreover, an independent project administrator will label the probiotics or placebo packs with unique numbers corresponding to random sequences in advance to achieve allocation concealment. According to the order of randomization, the distributor will distribute the treatment packs to the corresponding volunteers.

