### Statistical analysis

First, the intention-to-treat (ITT) analysis will be conducted between the two groups, including all the intended participants who do or do not complete the follow-up. Then, per-protocol (PP) analysis will be conducted in the four-subgroup datasets according to compliance (100%, ≥ 80%, 60–80%, and < 60%) to validate the robustness of the results. The datasets will be analysed as described below.

With a randomized block design, the nonparametric rank sum test and Friedman M test will be performed to analyse the difference in each outcome measure at each time point (see “Intervention Outcome Measures” for details) between the two groups, including the GM analysis, RDQ score, GSRS score, faecal metabolomics, and BMI. The significance level will be set to *P* = 0.05. Next, the paired Wilcoxon signed-rank test will be performed for pairwise intragroup comparisons to analyse the change trends for each outcome measure before, during, and after the probiotic intervention. The significance level will be set at *P* = 0.05/[k(k-1)/2], where k is the number of groups in the comparison. For analysis of the oesophagitis grade, the diagnosis of LA-B at baseline and LA-A at week 12 indicates that the patient's oesophagitis grade will have decreased by one level. If the grade is LA-C at baseline and LA-A at 12 weeks, the patient’s oesophagitis grade will have decreased by 2 levels. The number of oesophagitis grades reduced by 1 and 2 levels in each group will be calculated. Then, a chi-square (*χ*^2^) test will be performed. AE rates in the two groups will be compared by the *χ*^2^ test or Fisher’s exact probability test based on the occurrence frequency of AE, and the difference in treatment compliance will be also examined by the *χ*^2^ test.

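### The Friedman M test is listed as a between-group test but cannot compare two independent arms, and the valid rank-sum test beside it leaves out the day-0 value

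*Protocol article*

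**What the plan says.** The Statistical analysis section of the protocol article opens its test list with "With a randomized block design" and continues that "the nonparametric rank sum test and Friedman M test will be performed to analyse the difference in each outcome measure at each time point". The contrast is "between the two groups, including the GM analysis, RDQ score, GSRS score, faecal metabolomics, and BMI". Both tests are therefore assigned to the arm comparison for every listed outcome, including the primary one. For these tests, "The significance level will be set to *P* = 0.05".

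Change from baseline appears only in the next step. Paired signed-rank tests compare visits within each arm, at 0.05/[k(k-1)/2].

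Randomization and blinding describes individual allocation to two parallel arms: a computer-generated sequence is "used to randomly assign the unique number (representing a volunteer) to the probiotic group or placebo group". The Abstract defines the primary measure as the change in the gut microbiome. Primary outcome lists stool sampling at weeks 0, 4, 8 and 12. Sample size calls the trial a superiority study and rests on a week-12 difference between groups.

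**The concern.** The Friedman test needs a block whose members are measured under every condition being compared. In this trial nobody is measured under both probiotic and placebo, and the article describes no matched sets. Permuted blocks in the allocation list, if used, would not supply them. The only natural block is the patient, with visits as the conditions, and the question tested is then whether values differ over time. Both arms take rabeprazole in weeks 1–8 and stop it for weeks 9–12, so a shared time course is plausible. As the section is written, a significant Friedman result could be reported as a difference between groups when it reflects the common treatment.

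That leaves the rank-sum test as the only named test that compares the arms. It is applied to values at each visit and not to change or to a baseline-adjusted value. The measure named as primary, change, thus has no stated between-arm test, while change within each arm does. A significant change in one arm and not in the other does not establish a difference between arms, which is what a superiority study has to show.

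**Working it through.** **Inputs.** From Sample size: Chao1 difference 145 at week 12, SD 230, α = 0.025, β = 0.20, up to 20% loss, 60 recruited per arm. Evaluable per arm at 20% loss: 60 × 0.8 = 48. Assumed, because the article does not give them: the correlation r between baseline and week 12 (0.3, 0.5, 0.7), normally distributed data, and a within-patient correlation of 0.5 between visits in the Friedman simulation.

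**The plan's own figure.** n per arm = 2[SD(z₁₋α/₂ + z₀.₈₀)/difference]². With two-sided 0.025 this is 2 × [230 × (2.241 + 0.842)/145]² = 47.8, against 47.9 stated. The same formula gives 15.0 for Shannon (difference 0.9, SD 0.8), as stated. At two-sided 0.05 it gives 39.5 for Chao1, which does not match. The design calculation is therefore an unadjusted comparison of two independent groups at week 12, at two-sided 0.025. The analysis section tests at 0.05, so both levels are shown below.

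**What Friedman detects.** Simulated with 48 per arm, four visits, patient as block, both arms pooled, tested at 0.05:

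- Both arms follow the same course (0, −0.4, −0.4, 0 SD at weeks 0, 4, 8, 12) with no treatment effect: rejected in 99% of runs. Within a single arm of 48 the figure is about 81–82%.
- The arms differ by a constant 145/230 = 0.63 SD at every visit with no time effect: rejected in about 5% of runs, the nominal level.

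The second case is a demonstration, since randomised arms should not differ at day 0. It shows that ranking within patients removes any difference in level between arms. A probiotic effect that grew after day 0 would move the statistic, but a rejection could not be told apart from a shared time effect.

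**What the day-0 value is worth.** Standardised difference d = 145/230 = 0.630. Baseline adjustment multiplies the residual variance by 1 − r², so the SD becomes 230√(1 − r²) and d becomes 0.630/√(1 − r²). Power uses the noncentral t distribution; the rank-sum figure is from 20,000 simulated trials.

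| Analysis, 48 per arm | Residual SD | d | Power, two-sided 0.025 | Power, two-sided 0.05 |
|---|---|---|---|---|
| Rank-sum, unadjusted | 230 | 0.630 | 77% | 85% |
| t-test, unadjusted | 230 | 0.630 | 79% | 86% |
| ANCOVA, r = 0.3 | 219 | 0.661 | 83% | 89% |
| ANCOVA, r = 0.5 | 199 | 0.728 | 90% | 94% |
| ANCOVA, r = 0.7 | 164 | 0.883 | 98% | 99% |

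About two points of the gain come from moving from ranks to a parametric test on normal data; the rest comes from baseline.

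Testing raw change scores would be a poorer remedy. Their SD is 230√(2(1 − r)), that is 272, 230 and 178 at r = 0.3, 0.5 and 0.7, so at r = 0.3 they do worse than no adjustment.

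**The case against.** The strongest reply is that the Friedman wording is a drafting slip. The next step in the section is pairwise within-arm signed-rank tests with a Bonferroni-type threshold, which is the usual follow-up to a Friedman test across visits. The authors may have meant rank-sum between arms and Friedman across visits. That is plausible and makes the repair small, but the sentence as printed assigns Friedman to the between-group contrast, so it still needs correcting.

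A second reply is that leaving out baseline is a choice about efficiency, consistent with a sample size that is also unadjusted. At the 0.05 level of the analysis section, the rank-sum test has about 85% power with 48 per arm, above the 80% target. This stands: the omission costs precision, not validity. It does not answer the mismatch between a primary measure defined as change and between-group tests that never use day 0.

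Several stronger readings are tempting, and the article does not support them:

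- *The rank-sum test is invalid here.* It is designed for two independent samples and is a correct test at any one visit.
- *Baseline is ignored altogether.* It is used in the within-arm tests; it is missing only from the between-arm contrast.
- *Non-completers are dropped, contrary to intention to treat.* The population is described as "including all the intended participants who do or do not complete the follow-up", and no exclusion is stated. A test at one visit needs a value at that visit, but handling of missing data may sit in an analysis plan that is not shown. Patients lost later still count in the week 4 and week 8 tests if sampled then.
- *The randomization and analysis sections contradict each other on blocking.* The former says that "a random sequence will be generated by the computer software R 4.1.0 and used to randomly assign the unique number"; it neither describes nor denies blocks, a detail that an article may leave out.

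**Conclusion.** The point holds in two parts of unequal weight. The firm part is that Friedman is misassigned. It cannot compare two independent arms, and used across visits it answers a question about time. This follows from the design and does not depend on the simulation settings, which only illustrate it.

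The second part is that the between-arm comparison does not use a baseline already collected, although change is the primary measure. The gain is about 6, 13 or 21 percentage points of power at two-sided 0.025 (77% to 83%, 90% or 98%) and about 4, 9 or 14 points at two-sided 0.05 (85% to 89%, 94% or 99%). It rests on the assumed correlations, normal data, the plan's difference and SD, and 48 evaluable per arm. A rank-based adjusted analysis would gain somewhat less on normal data. The planned 120 participants remain enough.

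**What to change.** In Statistical analysis, delete the Friedman M test from the between-group sentence. If it is kept, label it as a within-arm test across visits with the patient as block, and state that it is not evidence of a difference between arms.

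For Chao1, Shannon, RDQ, GSRS and BMI, make the between-arm result at week 12, the time point of the Sample size section, a baseline-adjusted comparison. Two forms would serve: ANCOVA with the day-0 value as covariate (rank-based if the outcome is skewed), or a repeated-measures model with baseline as covariate, which also uses the week 4 and week 8 values. Keep the unadjusted rank-sum test at week 12 as a sensitivity analysis, and present the within-arm signed-rank tests as descriptive of time course.

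The cost is a revised paragraph and a slightly more complex model. No new data, visits or participants are needed. The choice should be fixed before unblinding.

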**Method:**

This is a randomized, double-blind, placebo-controlled trial. A total of 120 eligible patients with GERD will be randomized into the experimental group or the control group. The treatment includes two phases: the initial treatment period lasts 8 weeks (weeks 1–8), and the maintenance treatment period lasts 4 weeks (weeks 9–12). During the initial treatment period, the experimental group will take rabeprazole and LiHuo probiotics, and the control group will take rabeprazole and a probiotic placebo; during the maintenance treatment period, the experimental group will take LiHuo probiotics, and the control group will take a probiotic placebo. The primary measure is the change in the GM. The secondary measures are the Reflux Disease Questionnaire (RDQ) score, Gastrointestinal Symptom Rating Scale (GSRS) score, faecal metabolome (FM), body mass index, Los Angeles grade of oesophagitis, adverse event (AE) rate and treatment compliance. Each outcome indicator will be assessed at day 0 (before administration), day 28 and/or 56 (during administration), and day 84 (end of administration) to reveal intragroup differences. AEs will be monitored to assess the safety of LiHuo probiotics.

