### To minimize confounding interventions

 Prohibited treatments during the study. Probiotics, prebiotics, and foods containing probiotics (such as yogurt) other than those used in this study; Drugs for gastro-oesophageal reflux, such as acid inhibitors, antacids, gastric mucosal protectors, prokinetics, and equivalent drugs [19, 20] (see Additional file 1: Appendix 4) other than the study drug; Antibiotics and probiotics should be taken 2 h apart; Participants will be instructed to avoid spicy foods and to abstain from smoking or drinking during the study.

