### Secondary outcome

RDQ score: The RDQ (see Additional file 1: Appendix 5) includes 4 symptoms: heartburn, acid reflux, regurgitation, and noncardiac chest pain. Each symptom is rated on a 0–5 scale based on its frequency and severity in the last week. The total score is 40, and a higher score is associated with more severe symptoms. RDQ ≥ 12 indicates GERD [18, 21]. The RDQ will be used to evaluate reflux-related symptom scores on day 0 (week 0), day 28 (week 4), day 56 (week 8), and day 84 (week 12).GSRS score: The GSRS (see Additional file 1: Appendix 6) is a self-rating scale that includes 15 items in 5 subscales (abdominal pain, acid reflux, dyspepsia, constipation, and diarrhoea). Each item is rated on a Likert scale ranging from 0–3 (none, mild, moderate, mild) based on the severity of symptoms in the last week. The total score is 45, and a higher score is associated with more severe symptoms [22–24]. The GSRS will be used to evaluate gastrointestinal disease symptom scores on day 0 (week 0), day 28 (week 4), day 56 (week 8), and day 84 (week 12).Faecal metabolome (FM): Based on the faeces, FM from day 0 (week 0), day 28 (week 4), day 56 (week 8), and day 84 (week 12) will be evaluated. Stool samples will be extracted using the protein precipitation method, and the supernatant will be transferred to sample vials for mass spectrometry combined with liquid chromatography (LC–MS/MS) analysis. The original data will be subjected to peak alignment, retention time correction, and peak area extraction through the XCMS-Plus program. The structure of metabolites will be identified by accurate mass matching (< 5 ppm) and two-level spectrum matching, and the METLIN database will be retrieved. Missing values > 50% in the group will be deleted, and the data will be normalized. Multidimensional statistical analysis will then be carried out, including unsupervised principal component analysis (PCA), supervised partial least squares discriminant analysis (PLS-DA) and potential differential metabolite analysis. Metabonomic analysis could further identify the potential differential metabolites of probiotics in the treatment of GERD, and correlation analysis between the gut microbiota and metabolites could be performed.Change in the Los Angeles (LA) grade of oesophagitis: According to gastroscopy, the change in the LA grade of oesophagitis will be evaluated.Body mass index (BMI): BMI = weight (kg)/height (m)^2^. BMI will be measured in the morning using the same weight and height scales at each visit. Participants will be instructed to wear light clothing and take off their shoes (standing barefoot or wearing socks no thicker than 0.1 cm) during the weight and height measurements.AE rate: all the AEs collected as described below will be used to calculate the AE rate in each group.Treatment compliance will be monitored as described in the “Volunteer compliance monitoring” section. Although efforts have been made to promote treatment compliance, there may still be differences between the two groups due to AEs.

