
### Safety evaluation

AEs will be evaluated with blood tests, urine analysis, and stool tests (> 2 × ULN or < 2 × LLN); liver tests (ALT, AST, total bilirubin); renal tests (Scr, blood urea nitrogen); and ECG. AEs may be related or unrelated to the study interventions.At each visit, the patients will be asked about any AEs with nondirective questions. Patients may also voluntarily report AEs.Severe adverse events (SAEs) are events that occur after the study interventions are provided and result in hospitalization, prolonged hospitalization, disability, impaired ability to work, threats to the patient’s life, or death. All SAEs must be reported to the Ethics Committee of the hospital and the sponsor. Participants with SAEs will discontinue the interventions.Treatment-related AEs must meet the following criteria: a reasonable temporal/causal relationship with the treatment; side effects unrelated to comorbidities or concomitant medications; improvement or resolution of AE symptoms after treatment discontinuation; and causality can be explained with a pharmacological, biological, or phenomenological mechanism.

Drug-related AEs: possible adverse reactions experienced while taking rabeprazole include allergies (rash, itching, urticaria), abnormal blood test results, abnormal biochemical parameters, high blood pressure, gastrointestinal symptoms (constipation, diarrhoea, abdominal distension, nausea, lower abdominal pain, bitter taste in the mouth), headache, dizziness, palpitations, fever, fatigue, hypoesthesia, dry mouth, blurred vision, and vomiting. Possible serious adverse reactions include shock, interstitial nephritis, liver dysfunction, jaundice, anaemia, and hyponatremia. Possible adverse reactions to probiotic ingestion include diarrhoea, constipation, and weight loss.

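### The only stated between-arm BMI test compares raw BMI at each visit and does not use Visit 1 BMI; it is valid but wastes precision that is free to recover

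*Protocol article*

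**What the plan says.** All references are to the protocol article.

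- **Between-arm test (Statistical analysis).** A "nonparametric rank sum test and Friedman M test will be performed to analyse the difference in each outcome measure at each time point", applied "between the two groups, including the GM analysis, RDQ score, GSRS score, faecal metabolomics, and BMI", at a significance level of 0.05.
- **Use of baseline (Statistical analysis).** In the next step, "the paired Wilcoxon signed-rank test will be performed for pairwise intragroup comparisons to analyse the change trends for each outcome measure". The Abstract (Method) gives the same purpose for repeated assessment: it runs to "day 84 (end of administration) to reveal intragroup differences".
- **BMI (Secondary outcome; Table 1).** BMI is listed under the secondary outcome measures and marked at Visits 1 (Day 0), 2, 3 and 4. Measurement is standardised: "BMI will be measured in the morning using the same weight and height scales at each visit".
- **Weight loss (Safety evaluation).** "Possible adverse reactions to probiotic ingestion include diarrhoea, constipation, and weight loss".
- **Lifestyle advice, both arms (To minimize confounding interventions).** "Participants will be instructed to avoid spicy foods and to abstain from smoking or drinking during the study".

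For the oesophagitis grade, the same Statistical analysis section does define each patient's change from baseline to week 12 and compares it between arms. BMI has no such step.

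**The concern.** Adult BMI differs widely between people and usually moves little within a person over 12 weeks. A raw comparison at one visit is therefore dominated by stable differences between patients, which Visit 1 BMI would largely remove. The Friedman test does not help. If patients are the blocks, it compares visits and not arms, and no matched blocks across two independent arms are described.

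The paired tests do use Visit 1, but only within an arm. They are not a randomised comparison and cannot formally separate a probiotic effect from a change that both arms share, for example after advice to stop drinking and smoking. If the probiotic lowered weight slightly, the report could show a significant paired loss on probiotic that cannot be attributed to it, next to a non-significant between-arm test that is easily misread as reassurance.

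**Working it through.** **Inputs from the article.** 60 patients per arm; with the allowed 20% loss, 60 × 0.8 = 48. Between-arm level 0.05, taken as two-sided. BMI at Visits 1–4.

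**The plan's own figure.** None is given for BMI. The sample size for Chao1 (difference 145, SD 230, α 0.025, power 80%) reproduces with n = 2[SD(z_α + z_β)/δ]² and two-sided α: 47.83 against the stated 47.9. The sample size is not in question; it only fixes the number of patients available.

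**Assumptions (not in the article).** BMI SD 3–4 kg/m²; correlation r of Visit 1 with follow-up 0.90–0.98; true loss 0.37 kg/m², which at a height of 1.65 m is 0.37 × 1.65² = 1.0 kg.

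**Step 1: relative precision (no SD or effect size needed).** Relative to the raw comparison, the variance is 1−r² for ANCOVA and 2(1−r) for a change score. The raw comparison therefore needs this many times the patients:

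| r | against ANCOVA, 1/(1−r²) | against change, 1/[2(1−r)] |
|---|---|---|
| 0.90 | 5.3 | 5 |
| 0.95 | 10.3 | 10 |
| 0.98 | 25.3 | 25 |

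The change score beats the raw comparison only if r exceeds 0.5. ANCOVA does not depend on that threshold. At r 0.80 the ANCOVA ratio is 2.8.

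**Step 2: smallest difference detectable with 80% power.** (1.96 + 0.842) × SD × √(2/m), where m = n × 3/π for a rank test and m = n for ANCOVA, with SD multiplied by √(1−r²) for ANCOVA.

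| Patients per arm | raw rank sum | ANCOVA, r 0.95–0.98 |
|---|---|---|
| 60 | 1.57–2.09 kg/m² (4.3–5.7 kg) | 0.31–0.64 kg/m² |
| 48 | 1.76–2.34 kg/m² (4.8–6.4 kg) | 0.34–0.71 kg/m² |

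**Step 3: power for a 0.37 kg/m² loss.** Worked case with SD 3.5, r 0.95, 60 per arm:

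- Raw rank sum: m = 57.3, SE = 3.5 × √(2/57.3) = 0.654, 0.37/0.654 = 0.57, power 9%.
- Rank sum on change: SD = 3.5 × √0.10 = 1.107, SE = 0.207, ratio 1.79, power 43%.
- ANCOVA: SD = 3.5 × √(1−0.9025) = 1.093, SE = 1.093 × √(2/60) = 0.200, ratio 1.85, power 46%.

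Simulation of the same case (10,000 trials) gave 8.4%, 42.4% and 44.9%. Over SD 3–4 and 48–60 per arm:

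| r | raw rank sum | rank sum on change | ANCOVA |
|---|---|---|---|
| 0.90 | 7–11% | 17–32% | 18–34% |
| 0.95 | 7–11% | 27–54% | 29–57% |
| 0.98 | 7–11% | 58–90% | 61–92% |

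The ANCOVA range at r 0.90 is from the formula: SD 4, 48 per arm, SE = 4 × 0.436 × √(2/48) = 0.356, ratio 1.04, 18%; SD 3, 60 per arm, SE = 3 × 0.436 × √(2/60) = 0.239, ratio 1.55, 34%.

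**Step 4: validity.** With no true difference, the simulated rejection rate of the raw rank sum test was 4.5–5.3%. The test is sound.

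**Step 5: what the paired tests can show.** For SD 3–4, r 0.95–0.98 and 60 per arm, the paired test in the probiotic arm detects a 0.37 kg/m² loss in 30–97% of trials at 0.05/6 (taking k as the four visits). If both arms lose 0.37 kg/m², it is significant just as often (31–97%), while a between-arm rank sum test on change rejects in 4–6%.

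**The case against.** **It is a valid test on an unpowered secondary outcome.** This stands. BMI is one of seven secondary measures, no BMI hypothesis or target difference is given, and the trial is sized on alpha diversity. It limits the importance of the point but does not justify leaving out a baseline that is already measured.

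**The safety framing goes further than the article.** This stands in part. Table 1 lists BMI as a secondary outcome and not as a safety measure, and no section makes detecting a 1 kg loss its purpose. AEs are asked about at each visit and their rates are compared between arms. A reader might infer that the plan would let weight loss go undetected as a safety matter; the article does not support that. Still, a comparison of overall AE rates would not isolate a small shift in weight.

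**The power contrast depends on r.** This stands. With SD 3.5 and 60 per arm, power rises from 9% to 80% on change only at r 0.98, the top of the assumed range; at r 0.95 it reaches 42%. At r 0.90 the absolute gain is small.

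**The control arm is also tested within itself.** True: the paired tests are not confined to the probiotic arm, so a shared loss would be visible descriptively. Reading two separate P values side by side is still not a test of the difference between arms.

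**Only a journal article is shown.** A reader might infer that no baseline-adjusted BMI analysis exists anywhere. The article cannot show that. But it fixes the test, the outcome, the time points and the level, so the point concerns a stated choice and not an omission.

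**Conclusion.** The point holds as one of efficiency. The single between-arm BMI comparison that the article states ignores Visit 1 BMI and so needs about 5, 10 or 25 times the patients of a baseline-adjusted one at r 0.90, 0.95 or 0.98. These ratios rest only on the assumed correlation; the power figures rest also on the assumed SD of 3–4 kg/m² and loss of 0.37 kg/m².

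Two stronger readings are tempting and wrong. First, the raw comparison is not biased or invalid: randomisation protects it and its type I error is nominal. Second, Visit 1 BMI would not settle whether a 1 kg loss occurs: power on change is 17–32% at r 0.90 and mostly below 50% at r 0.95. The firmer benefit is in estimation. With 60 per arm, the 95% CI half-width, 1.96 × SD × √(2/60), is 1.07–1.43 kg/m² for raw BMI; multiplied by √(1−r²), it is 0.21–0.45 kg/m² for ANCOVA at r 0.95–0.98.

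The change is worth making, but it concerns a secondary outcome only.

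**What to change.** In Statistical analysis, take BMI out of the list for the raw per-visit test and add:

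> BMI at weeks 4, 8 and 12 will be compared between arms by ANCOVA adjusting for Visit 1 BMI, with week 12 as the main time point; the arm difference will be reported with its 95% CI. Within-arm paired BMI tests are descriptive.

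This names one method, so it leaves no choice to be made after the data are seen, and it replaces the raw-BMI comparison without adding to it. The cost is a sentence or two: no new data, visits or patients, because Table 1 already schedules BMI at Visits 1–4. The remaining limit is that power for a 1 kg loss may still be modest, so the interval should be read and not the P value alone.
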